# Education Program for Enhancing Health Care Students’ Attitudes Toward People Living With Dementia: Protocol for a Single-Arm Pre-Post Study

**DOI:** 10.2196/62654

**Published:** 2024-09-18

**Keywords:** ageism, dementia, health professional, education program, long-term care

## Abstract

**Background:**

Health care students are instrumental in shaping the future of dementia care. Cultivating a positive attitude and understanding toward people living with dementia is crucial for diminishing the stigma associated with the condition, providing effective and person-centered care, and enhancing the quality of life for people living with dementia. Educational programs about dementia are increasingly recognizing the potential of gaming tools.

**Objective:**

This study aimed to evaluate the effectiveness of gaming-based dementia educational programs in improving attitudes toward people living with dementia among health care students.

**Methods:**

This single-arm pre-post study will be conducted among health care students in Indonesian universities. This educational program based on gaming tools will consist of a lecture on dementia, the use of N-impro (gaming tool), and the enactment of short dramas depicting desirable and undesirable communication with people living with dementia behaviors. We will assess attitudes toward people living with dementia, intention to help people living with dementia, knowledge of dementia, and the stigma associated with people living with dementia. The gaming-based dementia education program will be integrated into the curriculum of the health care students. The program will be implemented once with a duration of 90 minutes.

**Results:**

Data collection will occur from August 2023 to March 2024. Analysis of the data will be finalized by May 2024, and the outcome will be determined by July 2024. The impact of the gaming-based dementia educational program on improving attitudes toward people living with dementia will be reported. The study findings will be published in a peer-reviewed journal.

**Conclusions:**

The gaming education program demonstrates significant potential in enhancing attitudes toward people living with dementia across various countries, introducing an innovative method for the community-based support of people living with dementia.

**Trial Registration:**

ClinicalTrials.gov NCT06122623; https://clinicaltrials.gov/study/NCT06122623

**International Registered Report Identifier (IRRID):**

DERR1-10.2196/62654

## Introduction

The global increase in the aging population has increased the number of people living with dementia [1]. In Indonesia, the adjusted weighted people living with dementia rate is 27.9%, indicating a potential population of over 4.2 million people living with dementia [2]. Consequently, global policies have been established to foster a “dementia-friendly” society [3,4]. Dementia-friendly initiatives aim to enhance the quality of care for patients with dementia [5]. Distinguishing ageism from carefully reasoned clinical decisions can be challenging [6]. Health care professionals such as medical doctors, public health workers, nurses, dentists, pharmacists, and nutritionists may inadvertently perpetuate ageism, as it can be deeply embedded in daily procedures. As a result, older adults may not receive the same level of care as younger patients [7]. Therefore, health care professionals must improve their ability to provide dementia care to address the diverse needs of older adults and combat ageism.

A previous study found that medical students had neutral attitudes toward older individuals and lacked knowledge about dementia [8]. Whereas, a study in Indonesia found low knowledge but high attitudes toward dementia among nursing students [9]. Bachelor’s degree courses are offered to help health care professionals understand health care subjects, including holistic care for older adults with dementia. Health care students may struggle to care for older adults with dementia due to a lack of understanding of how to respond to specific symptoms of dementia and challenges in visualizing actual care scenarios [10]. Thus, it is necessary to pursue effective educational methods that enhance knowledge and attitudes toward older adults.

Health care professionals can provide quality care by combining integrated learning, critical thinking, and optimal decision-making skills. The integration of simulation into the educational process facilitates the attainment of this goal. A previous study has suggested that simulated education is beneficial for content that is challenging to convey through traditional classroom instruction [11]. One such method of simulation education is a gaming-based education program, which allows students to engage with and enjoy the learning process [12,13]. The implementation of dementia education through a game- and simulation-based program has been shown to effectively enhance knowledge and attitude toward dementia among health care students [14-17]. Therefore, an educational approach that introduces dilemmas through gaming, is needed [18].

In recent years, we have developed a dementia gaming-education program known as N-impro [19,20]. This program is designed to influence attitudes toward supporting older adults and foster community networks that promote an age-friendly environment within Japanese communities. Given the rapidly increasing demand for health care professionals and long-term care facilities to care for the older adults in Indonesia [21], the N-impro program will be adapted for health care students in Indonesia with necessary modifications to improve attitudes toward supporting older adults. Therefore, this study aims to assess the effectiveness of gaming-based dementia educational programs in enhancing health care students’ attitudes toward people living with dementia.

## Methods

### Study Design

This study will use a single-arm pre-post design to assess the effectiveness of gaming-based dementia educational programs for health care students. The study will be conducted in collaboration with the Faculty of Health at an Indonesian University. The programs will be integrated into courses related to dementia care, such as the Gerontological Nursing Care course, the Psychiatric Nursing course, and the Health Assessment course. Participation in the study is open to all students in these classes. However, there will be no penalties for students who choose not to participate. The study will continue until participant inclusion is completed, which is anticipated to be around March 2024.

### Participants and Settings

Participants in this study will be health care students at an Indonesian University. For this study, we will invite nursing and public health students. A participant must meet the following inclusion criteria: they must be a health care student enrolled in the semester for which we have designated the course for the implementation of this educational program. For instance, nursing students at Airlangga University will be selected from those in the fifth semester. While public health students are in the sixth semester, both are third-year grade health care students with class topics related to dementia. Prospective participants will be assigned a new ID number to ensure their student ID numbers remain confidential. The sample size was calculated using a power analysis for differences between two dependent means (matched pairs). The total sample size is 68 health care students with an effect size of *d*=0.5 (Reference from N-impro study: *d*=0.5, α=0.05, power=0.80). In conducting a matched pair *t* test analysis, this study will collect sufficient data from the participants; the sample size will exceed the calculated sample size.

This study will be conducted at Indonesian universities with health-based faculties. Health education activities will be implemented in various classrooms within the university. Each classroom will accommodate approximately 50 participants and will be equipped with chairs and tables to facilitate discussion. The classrooms will be divided into 4 parts, each comprising up to 10 chairs.

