### Data Analysis

Statistical analyses will be performed as follows: initially, descriptive analyses will be conducted to outline the characteristics of the participants. Subsequently, we will evaluate changes in total and subscale scores for attitudes toward people living with dementia, intention to help people living with dementia, knowledge of dementia, and stigma associated with people living with dementia before and after the program using paired *t* tests and the Wilcoxon rank sum test. To determine the effectiveness of the program, we will calculate effect sizes using Cohen *d*, classifying differences between pre- and postprogram scores as small (*d*=0.2), medium (*d*=0.5), or large (*d*=0.8). We will set the threshold for statistical significance at *P*<.05 (2-tailed). The statistical analysis will be conducted using IBM SPSS Statistics (version 26.0).

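### The calculated sample size of 68 students does not follow from the stated matched-pairs inputs, which give 34; the discrepancy is on the safe side

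*Protocol article*

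**What the plan says.** Participants and Settings names the method, a "power analysis for differences between two dependent means (matched pairs"), and gives every input: "Reference from N-impro study: *d*=0.5, α=0.05, power=0.80". It reports the result as follows: "The total sample size is 68 health care students with an effect size of" d=0.5. It then says that "the sample size will exceed the calculated sample size", so 68 is presented as the output of the calculation and not as a figure already inflated.

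Study Design describes one arm measured before and after, so each student contributes one pair. Data Analysis compares scores "before and after the program using paired *t* tests and the Wilcoxon rank sum test" and sets significance at P<.05, two-tailed. The article states no dropout allowance, pre-post correlation, multiplicity adjustment or design effect for the sample size.

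**The concern.** The article gives a method, a full set of inputs and a result, so the result can be checked, and it does not reproduce. This is a figure stated wrongly, not a detail left to a fuller document.

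The sample-size statement is where the plan says what effect it is sized to detect on the primary outcome, attitude toward people living with dementia. As printed, a reader would take d=0.5 to be the effect that 68 students detect with 80% power. On the stated method, 68 students reach that power at a clearly smaller effect. This bears on interpretation because Data Analysis grades results as small, medium or large at d=0.2, 0.5 and 0.8. A significant result could arise well below the medium effect named in the sample-size sentence.

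**Working it through.** **Inputs.** d=0.5, alpha 0.05, power 0.80, matched pairs and stated N=68, all from Participants and Settings. Two-sided testing comes from Data Analysis. One pair per student comes from Study Design. Because the named method is for dependent means, d is read as dz, the mean paired difference divided by the SD of those differences.

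**Attempt to reproduce 68.** Normal approximation: n = ((1.960 + 0.842)/0.5)² = 7.85/0.25 = 31.4, so 32.

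Exact calculation: noncentral t with n − 1 degrees of freedom and noncentrality dz·√n.

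| n | noncentrality 0.5·√n | two-sided power |
|---|---|---|
| 33 | 2.872 | 0.795 |
| 34 | 2.915 | 0.808 |
| 68 | 4.123 | 0.982 |

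The smallest n reaching 0.80 is 34. The stated 68 is not reproduced; 68/34 = 2 exactly.

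**What 68 delivers.** Solving the same power function for 80% power at n=68 gives dz=0.345.

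**Other single routes to 68**, each changing one element of the base case:

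| Variant | Result |
|---|---|
| One-sided paired t | 27 |
| Power 0.90 / 0.95 / 0.98 | 44 / 54 / 67 |
| Alpha 0.05/4 = 0.0125 | 48 |
| Wilcoxon efficiency 0.955 or 0.864 applied to 34 | 36 or 40 |
| Two independent groups, two-sided | 64 per group, 128 in total |
| Dropout allowance of 20% | 34/0.8 = 42.5, so 43 |
| Dropout needed to reach 68 | 1 − 34/68 = 50% |

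Only a 50% dropout allowance gives 68. None is stated, and Table 1 places both questionnaires within the same session.

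**Sensitivity to the meaning of d.** If d=0.5 were standardised by the raw-score SD (equal before and after), then dz = 0.5/√(2(1 − ρ)), where ρ is the pre-post correlation. The article gives no ρ, so these values are assumptions:

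| ρ | dz | n, two-sided, 80% power |
|---|---|---|
| 0 | 0.354 | 65 |
| 0.1 | 0.373 | 59 |
| 0.3 | 0.423 | 46 |
| 0.5 | 0.500 | 34 |
| 0.8 | 0.791 | 15 |

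No non-negative correlation gives 68 by itself. Adding a second unstated assumption comes close: 65/0.955 = 68.1 (ρ=0 with one Wilcoxon correction) or 59/0.864 = 68.3 (ρ=0.1 with another).

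**The case against.** The strongest reply is that the error does no harm. The printed figure is a minimum, recruitment is meant to pass it, and all students in the chosen classes may take part. At 68 the study exceeds its 80% target for d=0.5. All of this stands, and it sets the severity. A reader might infer from the mismatch that the study is underpowered. The figures show the opposite: power is 0.98, not below 0.80.

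A second reply is that d may not be dz. It comes from a previous N-impro study that is not shown, and Data Analysis uses Cohen d without naming a standardiser. This stands in part: 34 is conditional on the dz reading, which is the natural one for the named test. It does not rescue 68. Even zero correlation gives 65, and zero is implausible for the same students answering the same scale within one session. Reaching about 68 takes a further correction that the article does not mention.

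A third point concerns cause. Because 2 × 34 = 68, a reader might infer that each pair was counted twice. The documents do not support that as fact. Since nursing and public health students are both invited, 34 in each group would also total 68, and that too is unstated. The text cannot separate these explanations. Nor can one claim that no combination of assumptions yields 68, given the two-assumption routes above. What survives is narrower: the stated method and inputs give 34, and nothing stated bridges the gap to 68.

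**Conclusion.** The point holds as a wrong stated figure of lower severity. On the plan's own method and inputs the calculated size is 34 complete pairs, and the article prints 68, which is twice as many. The result rests on three assumptions: d is the standardised mean paired difference, the test is two-sided as in Data Analysis, and students are independent. Under the same assumptions 68 students give power 0.98 at dz=0.5, or 80% power at dz=0.345. The error is conservative. It misstates what the study is sized to detect but leaves the primary comparison and the enrolment plan untouched. How 68 arose is unknown from the documents.

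**What to change.** Make one of these changes to the sample-size sentence in Participants and Settings:

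- Restate the calculated size as 34 students with complete pre and post scores (paired t test, two-sided alpha 0.05, dz=0.5, power 0.81), and keep the statement that recruitment will go beyond it.
- Keep 68 as the minimum and state what it delivers with independent students: power 0.98 at dz=0.5, or 80% power at dz=0.345.
- If 68 came from an assumption not printed, state that assumption, for example the standardiser of d and the pre-post correlation, so that the figure can be reproduced.

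In each case, say whether d is dz. Do not add a design effect or intraclass correlation afterwards to justify 68. With groups of 7–8, averaging 7.5, a doubling needs an ICC of 1/6.5 ≈ 0.15. The documents give no source for that value, which would simply be chosen to make the answer 68.

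The cost is one sentence. Enrolment, design and analysis do not change.

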### Recruitment

Prospective participants will be identified using information from the e-learning portal of the university. We will document the data of the students enrolled in the designated course for the execution of this educational program at the start of the odd semester for the 2023-2024 academic year. Individuals who meet the eligibility criteria will receive detailed communications about the study and invitations to participate in the program.

The course coordinator and principal investigator (PI) will comprehensively explain the learning plan or syllabus for the designated course at the beginning of the semester. Generally, an overview of the execution of the research session will be presented, and detailed research procedures will be presented shortly before the research begins. An announcement regarding the research implementation will be distributed approximately 1 week in advance, and the recruitment process will be conducted through a Google form. Following the explanation of the research procedure, potential participants can freely choose whether or not to participate in the research. Those who express interest will receive a new ID for this study and will be notified of the schedule and location of the educational program through a class announcement 3 days before it commences.

On the event day, prospective participants will gather at the designated venue and formally record their attendance by signing an attendance sheet with their newly assigned ID. The PI overseeing this research will clarify all study phases, highlighting the participants’ right to withdraw at any point. Participation in this research will be entirely voluntary. Students who choose not to participate will continue to receive standard dementia-related materials through the e-learning portal of the university, with the exception of the game-based education program. All participants who consent to participate will express informed consent at the beginning of the Google form. Furthermore, we will state that we would regard the completion and submission of the questionnaires as consent to participate.

### Implementation

The intervention of this study is a gaming education program, which will be conducted once for each participant. The program will be implemented at various times, with each session accommodating a maximum of 60 participants. These participants will be divided into small groups of approximately 7-8 individuals within the same room, each group led by a facilitator. The facilitators, who will be either research team members or health lecturers, will be recruited and trained jointly by the Japanese and Indonesian research teams. The program’s instructors include the PI of this study, assisted by a research team serving as co-instructors.

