### Data Collection

Data will be collected from November 2023 to March 2024 through an online questionnaire. Participants will be informed to prepare a mobile phone or personal computer before joining the class. For the online questionnaire, participants need to access the form, enter the required information, complete the questionnaire, and submit the form. Participants do not need to log into their Google accounts to access the link. They will only provide the new ID number at the beginning of the form. The link to the questionnaire will be shared through a QR code displayed on the classroom screen.

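### The planned paired tests and the sample size treat students as independent, although they are taught in facilitator-led groups; if changes correlate within groups or sessions, the two-sided 5% level is exceeded

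*Protocol article*

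**What the plan says.** Under Study Design: "This study will use a single-arm pre-post design to assess the effectiveness of gaming-based dementia educational programs for health care students". There is no control arm, so the primary conclusion rests on one mean change in attitude score and its standard error.

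Delivery is described under Implementation. The programme runs at several times, "with each session accommodating a maximum of 60 participants", and within each session: "These participants will be divided into small groups of approximately 7-8 individuals within the same room, each group led by a facilitator". The section on the gaming tool repeats the group size and the single facilitator, and describes the game as a discussion of dilemmas. Table 1 puts the posttest straight after the programme, in the same sitting.

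Under Data Analysis, "we will evaluate changes in total and subscale scores" by paired t tests and a Wilcoxon test at a two-sided 5% level. Group, facilitator and session do not appear.

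Under Participants and Settings: "The sample size was calculated using a power analysis for differences between two dependent means (matched pairs"), with the result "The total sample size is 68 health care students with an effect size of *d*=0.5" ("Reference from N-impro study: *d*=0.5, α=0.05, power=0.80"). Enrolment is expected to go above that number. The Limitations section discusses the missing control group but not clustering.

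**The concern.** Students who discuss the same dilemmas under the same facilitator, and answer the posttest minutes later in the same room, may change by similar amounts. Pairing removes stable differences between students. It does not remove correlation between the changes of students who shared a group or session.

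Where such correlation is positive, a standard error computed as if each student were independent is too small. The confidence interval for the primary outcome is then too narrow, the P value too small, and the result looks more reproducible across other groups and facilitators than it is. With no control arm, no comparison between arms is available to absorb shared group effects.

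This is not a matter of detail left to an analysis plan. The article names the tests and the sample-size method, and both assume independence.

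**Working it through.** **Inputs from the protocol.** n = 68, d = 0.5, two-sided 5%, power 0.80 (Participants and Settings; Data Analysis). Groups of 7-8 and sessions of at most 60 (Implementation). Rooms for about 50 (Participants and Settings).

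**Assumed.** The ICC of the change scores, which the protocol does not give. I use 0.01 to 0.15 for groups and 0.02 to 0.05 for sessions.

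**The plan's own figure.** An exact paired t calculation with d = 0.5, two-sided 5% and 80% power needs 34 pairs (power 80.8%). With 68 pairs the power is 98.2%. The stated 68 is therefore not reproduced; it equals 2 × 34. That is a separate matter, and I take 68 as stated below.

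**Group-level correlation.** Sixty-eight students make nine groups (5 × 8 + 4 × 7 = 68), with m about 7.5.

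- Design effect: DEFF = 1 + (m − 1) × ICC
- Effective n = 68 / DEFF
- Actual two-sided level = 2 × [1 − Φ(1.96 / √DEFF)]

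For ICC 0.05: DEFF = 1 + 6.5 × 0.05 = 1.325; effective n = 68 / 1.325 = 51; 1.96 / √1.325 = 1.70; level = 8.9%.

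The simulated columns use the nine groups above, with 20,000 to 40,000 runs per setting.

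| Assumed group ICC | DEFF | Effective n | Level, formula | Level, simulated paired t | Level, t test on group means |
|---|---|---|---|---|---|
| 0.01 | 1.065 | 64 | 5.8% | 6.0% | about 5% |
| 0.02 | 1.13 | 60 | 6.5% | 6.5% | about 5% |
| 0.05 | 1.325 | 51 | 8.9% | 8.7% | about 5% |
| 0.10 | 1.65 | 41 | 12.7% | 12.8% | about 5% |
| 0.15 | 1.975 | 34 | 16.3% | 16-17% | about 5% |

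**Session-level correlation.** With at most 60 per session, 68 students need at least two sessions. For two equal sessions of 34 and a session ICC of 0.02, DEFF = 1 + 33 × 0.02 = 1.66 and the level is 12.8%. With both sources present, simulation (two sessions, of 32 and 36 students) gives about 16% at group 0.05 plus session 0.02, and about 26% at 0.05 plus 0.05.

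**More students.** DEFF depends on cluster size, not on total n. A simulation of 201 students in 28 groups gives 8.6% at group ICC 0.05 and 12.6% at 0.10, much as before.

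**Power of the group-level analysis.** For d = 0.5 and nine groups, a t test on group means has power of about 0.88 (ICC 0.05), 0.80 (0.10) and 0.72 to 0.73 (0.15), without session correlation. The effective-n approximation is more favourable (0.88 at ICC 0.10) because it ignores that only 8 degrees of freedom remain.

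**What a group-level analysis leaves behind.** At session ICC 0.02 with two sessions and no group effect, the paired t test rejects a true null about 13% of the time, the t test on group means about 10%, and an analysis with session as a fixed effect about 11%. With so few sessions, neither alternative removes session-level error.

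**The case against.** The strongest reply is that the ICC of the change scores is unknown and probably low. The lecture is recorded and projected, the films are shown to everyone, each group gets the same cards in the same order, and facilitators are trained twice. In Table 1 the game takes 20 minutes, against 10 + 25 + 10 = 45 minutes of identical film and lecture. This stands: at a group ICC of 0.01 to 0.02 with no session effect, the level is only about 6% to 7%. It does not standardise the facilitator, the discussion or the room, so zero correlation is not assured.

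A second reply is that the conclusion would often survive. At d = 0.5, t = 0.5 × √68 = 4.12. Divided by √1.65 (ICC 0.10) it is 3.21, with P about 0.01 even on 8 degrees of freedom. That also stands if the effect is as large as planned; a smaller effect has less room.

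Three stronger readings are tempting and are not supported.

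- A reader might infer that the 5% level is certainly breached. Without an ICC, the documents show only that it is breached if the correlation is positive.
- A reader might infer that 68 is too few. At group ICCs of 0.05 to 0.10 the effective n is 51 to 41, above the 34 pairs that the stated inputs require.
- A reader might infer that group membership goes unrecorded, because of the sentence "They will only provide the new ID number at the beginning of the form". In context, that sentence contrasts the study ID with a Google login. The Recruitment section has students sign an attendance sheet under the study ID, so session at least should be recoverable, and group may be held elsewhere.

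**Conclusion.** The point holds in conditional form. The planned tests and the sample size assume independent students, while the described delivery gives reason to expect some correlation of changes within groups and possibly within sessions. The harm is to the standard error, interval and error rate of the primary outcome more than to power.

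Its size rests wholly on the assumed ICC: slight at the low end that the standardised content favours, and 9% to 13% at group ICCs of 0.05 to 0.10. Session correlation would matter more per unit of ICC, because sessions are several times larger than groups, and it is harder to correct because sessions may be few.

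This should be changed because the remedy is cheap. It is secondary to the lack of a control group, which the protocol acknowledges.

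**What to change.** 1. Hold session and small-group number against each study ID, for example on the attendance sheet, if this is not already done. If data collection has closed, recover them from the attendance and allocation records.
2. Make the primary analysis of the attitude change score a linear mixed model with a random intercept for small group and small-sample (for example Satterthwaite) degrees of freedom, or a t test on small-group mean changes. Keep the simple paired t test as a sensitivity analysis.
3. Report results by session. If session enters as a fixed effect, state that inference is limited to the sessions observed. A t test on group means contains no session term, so it is not equivalent to a model with session in it.
4. State an assumed ICC beside the sample size and report the estimated one.
5. If group cannot be recovered, say so as a limitation and show the primary result with its standard error multiplied by √DEFF over a stated ICC range.

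The cost is one recorded item per student and one further model. The interval becomes wider. At d = 0.5 with nine groups, power is about 0.88 (ICC 0.05), 0.80 (0.10) and 0.72 (0.15) before any session correlation, so at the top of the range it falls below the planned 0.80. Enrolling additional groups, as the protocol expects to do, would raise it.
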